### Recruitment and informed consent procedure

Patients will be recruited from an outpatient pulmonology clinic in Switzerland in daily clinical practice. Participants will provide written informed consent, provided that they have had sufficient time for consideration and the opportunity to ask questions. Important concepts will be highlighted via bulleted text. A checkbox will assess whether participants understand key consent information in the presence of study investigators. These consent forms will be collected and countersigned by the study investigators and stored securely in an access-controlled room. No financial compensation will be offered to participants.

We anticipate that withdrawal and discontinuation will be limited as the study offers the advantage of taking place in a single centre and during a single, short (i.e., 60 min) intervention period on the day of a routine clinical visit. In the case of withdrawal after informed consent, the individual’s data collected so far and related to the intervention will be destroyed/deleted. Any withdrawal and/or discontinuation will be justified and reported in final publications in anonymised form.

### Hypothesis and objectives

#### Primary hypothesis

We hypothesise that point-of-care digital lung auscultation and LUS have a clinically exploitable predictive performance for the detection of pathological acoustic and sonographic signatures in patients with ILD. Furthermore, we propose that these signatures are sufficiently unique to not only discriminate ILD patients from control subjects, but also from COPD and other respiratory diseases, and perhaps even to categorise the various severity grades and subtypes of ILD, when determined. We further hypothesise that the automated interpretation of lung auscultation and LUS by deep learning could match or outperform expert evaluation and standardise lung auscultation and LUS interpretation.

#### Primary objective

To collect a systematic sound bank of digital lung auscultation and images for the development of deep learning algorithms that predict pathological signatures of ILD in an adult population to: (1) discriminate ILD from non-ILD lung sounds and images; (2) predict ILD clinical severity; (3) differentiate ILD from COPD; and (4) possibly determine the subcategories of ILD (i.e., IPF versus NSIP).

#### Secondary hypothesis

International clinical practice guidelines recommend to suspect IPF and NSIP in the presence of velcro-like crackles [45] (and similarly for coarse crackles in COPD). However, there are few data indicating whether these sounds are associated with clinical, functional, and radiological characteristics upon ILD diagnosis [4, 46].

#### Secondary objective

To investigate whether velcro-like crackles labelled by human experts are associated with the aforementioned characteristics in patients with IPF and NSIP (and similarly for coarse crackles and COPD). The impact of the diseases on patients’ health-related quality of life will be measured with standardised questionnaires.

Our overall hypothesis is that the use of *DeepBreath* might substantially improve the early and accurate diagnosis of patients with chronic lung disease.

### Primary and secondary outcomes

The primary outcome is the diagnostic of ILD, both IPF and NSIP, versus control subjects or COPD. We will assess the predictive performance of the *DeepBreath* algorithm-evaluated lung auscultation and LUS in the following identification and risk stratification tasks as follows: (1) to discriminate ILD from control subjects (according to expert clinical diagnosis [42]); (2) to differentiate ILD from COPD; (3) to predict ILD clinical severity (according to a HRCT grading scale^1^ and lung function tests^2^); and (4) to differentiate the subcategories of ILD (such as IPF, NSIP) according to the gold standard diagnosis [2, 43, 44]).

Secondary outcomes are the clinical, functional and radiological characteristics of IPF, NSIP and COPD diagnosis. We will: (1) compare the predictive performance of human, expert-identified acoustic and LUS signatures in the above predictive tasks (Kappa coefficient); (2) assess diagnostic performance of a model trained to detect crackles; (3) explore the utility of adding clinical data (signs, symptoms, demographics, medical history and basic paraclinical tests) to the breath sound algorithms; and (4) determine the impact of the diseases on subjects’ health-related quality of life measured with the standardised King’s Brief Interstitial Lung Disease (K-BILD) [47], the COPD assessment test (CAT) [48], and the 36-item Medical Outcomes Study Short-Form Health Survey (SF-36) [49] severity assessment questionnaires.

### Study procedure

The study will be performed over a period of 6 months. Recruitment can be stopped before the anticipated end if the inclusion of 160 patients is reached before. A trained research nurse/doctor ([name]) will recruit the subjects during a single routine consultation in the outpatient clinic. This will include checking the selection criteria for each patient prior to study participation, obtaining written informed consent, administering questionnaires on demographic characteristics (age, sex, occupation, long-term exposure to occupational or environmental agents, etc.), relevant medical history, and symptomatic presentation (Additional file 1), which will be captured by an electronic case report form to be completed by the study coordinator on a tablet. The nurse/doctor will also administer the standardised K-BILD [47], CAT [48], and SF-36 [49] severity assessment questionnaires, and record lung sounds during 5–7 min with an electronic stethoscope in the same zones as LUS acquisition, as previously proposed by our group [40]. For the LUS examination using a standard point-of-care ultrasound device, an adapted version of our previous 10-point acquisition protocol [50] will be used, which involves scanning the anterior superior, anterior inferior, posterior superior, posterior inferior and lateral thorax regions. In addition, pulmonary functional tests (conducted with patients in a stable condition) will be collected, as well as chest X-rays with two incidences (posterior-anterior and lateral) and HRCT scans for IIP patients (within 12 months). Controls will not be exposed to a chest X-ray and/or CT scan unless required as part of their routine follow-up; cases will have undergone such imaging given that it is part of their diagnostic evaluation.

All LUS images and lung sounds captured will be digitally recorded and transferred via a secured internet connection together with relevant metadata to a secure server. For study quality control purposes, the quality of the image and the interpretation of a random sample of images will be evaluated retrospectively by an experienced radiologist. The images will be further used for secondary studies developing machine learning algorithms and AI for LUS diagnosis. As this study will take place during outpatient visits under usual conditions and with conventional diagnostic measurement tools, we do not expect any problems that would put participants at a greater risk than normal exposure in daily clinical practice.

#### Lung sound recording

The frequency range of normal lung sounds extends from below 100 Hz to 1000 Hz, with a sharp drop at approximately 100 to 200 Hz [51], whereas tracheal sound extends between 100 to 5000 Hz. In the lower band range (under 100 Hz), heart and thoracic muscle sounds overlap. Abnormal lung sounds (wheezing, rhonchi etc.) have characteristic frequencies and duration, differentiating them from each other [51]. In particular, fine velcro-like crackles are caused by explosive openings of the small airways, have a distinguishable high-pitched frequency of about 650 Hz, and a typical short duration of about 5 ms.

In this study, the lung sounds will be gathered digitally in all subjects with the same Eko CORE digital stethoscope (Eko Devices, Inc., CA, USA). Four anterior thoracic sites (superior and inferior bilaterally), 4 posterior sites (superior and inferior bilaterally),) and 2 lateral sites (right, left) will be auscultated per patient using the stethoscope. For each auscultation site, a 30-s digital recording will be acquired. Patients will be informed of the necessity to breathe deeply. All signals will be saved as 16-bit resolution, 4 kHZ-sampled WAV files. The built-in filter will range from 20 to 2000 Hz. Heart and thoracic muscle sounds, as well as other background low-frequency noises, will be filtered out through EKO software’s high-pass filters. Coded recorded sounds will be synced in real-time to a General Data Protection Regulation (GDPR)-compliant secured cloud-storage location. Random auscultatory recordings will be reviewed by the study investigators for quality control.

## AI algorithms

### Diagnostic and risk stratification algorithms

We will develop *DeepBreath*, a deep learning algorithm to detect the acoustic signatures of IPF, NSIP and COPD from lung sounds. While several state-of-the-art approaches will be tested, the general framework is summarised in Fig. 2. Digital lung auscultations will first be cleaned to crop non-biological frequencies and amplitudes generated by ambient noise not filtered by the stethoscope’s active noise cancelling. The sounds will then be divided into overlapping time windows of between 1 and 10 s and transformed to Mel Frequency Cepstral Coefficients (MFCCs). Several data augmentation techniques will be explored, such as amplitude scaling, pitch shift and random time shift. The effect of each pre-processing method will be tested and the best performing approach according to sensitivity and specificity will be reported. This dataset will then be fed into various deep learning networks (such as convolutional neural networks, Long Short-Term Memory models [LSTM], Transformer architectures, etc.). A prediction on each segment will then be aggregated to represent a patient (including all anatomic sites) and binary classification into positive *vs* negative for diagnostic results will be performed for ILD or control subjects, ILD or COPD, and (if ILD-positive) IPF or NSIP. The same prediction will also be made using LUS images. Risk stratification will use multiclass or regression according to scales obtained from clinical interpretation of LUS, lung function tests, HRCT imagery, K-BILD or CAT, and SF-36 quality of life questionnaires.

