### Population

Inclusion criteria are consecutive, consenting adult outpatients (> 18 years) with IPF (group 1), NSIP (group 2) and COPD (group 3) already diagnosed prior to the consultation (index) date. Probable and definitive IPF diagnosis will be made according to the Fleischner Society Consensus [42], NSIP diagnosis with the American Thoracic Society classification [2, 43], and COPD with the Global Initiative for Chronic Obstructive Lung Disease criteria [44]. Consenting, age-matched (± 2.5 years) individuals with normal lung function (spirometry, lung volume and transfer factor for carbon monoxide [TL_CO_]) followed in the outpatient clinic with a similar quality of electronic medical records, but for diseases other than the outcome of interest, will serve as the 1:1 control group (group 4). This latter group will comprise patients with obstructive sleep apnoea, follow-up of occupational lung diseases (miners, chemical workers, etc.), and follow-up of pulmonary nodules (considered benign after 2 years). Reasons for pulmonary follow-up among the controls will be reviewed and reported in a supplementary file. Identifying all cases with the outcome of interest and selecting controls for comparison is a more efficient and resource-sparing study design than a full cohort study. Exclusion criteria are: (1) patients who cannot be mobilised for posterior auscultation; (2) those known for severe cardiovascular disease with pulmonary repercussions; (3) patients known for a concurrent, acute, infectious pulmonary disease (e.g., pneumonia, bronchitis); (4) patients known for asthma exclusive from COPD; (5) patients with alpha-1-antitrypsin deficit; (6) a physical inability to follow procedures; and 7) inability to give informed consent.

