### Statistical analysis plan

For descriptive statistics related to the clinical data collected, all continuous variables will be reported as medians with their interquartile ranges. Binary and categorical variables distribution will be reported as proportions and percentages. To evaluate baseline demographic differences and outcomes differences between the case and control patients, conditional logistic regressions will be used to account for the matched design. Pearson’s and Spearman’s correlation coefficients will be used to assess the relationship between continuous variables normally and non-normally distributed, respectively. For the primary outcome, each task will be quantified using descriptive statistics (i.e., proportion and type of abnormalities), as well as the AUROC, sensitivity, specificity, positive predictive value, negative predictive value, and likelihood ratios (with 95% CIs over a fivefold cross-validation).

The diagnostic accuracy of each echographic sign will be assessed and sensitivity, specificity, positive predictive value, negative predictive value, positive likelihood ratio, and negative likelihood ratio with their 95% CIs will be calculated. To find the combination of echographic signs with the best diagnostic accuracy, we will compare the performance of several multivariable models, such as logistic regression, random forest and neural networks. Performance will be reported on a test set comprising 20% of the data in a tenfold cross-validation with 95% CIs. As a secondary objective, we will aim to compare the predictive performance of human expert-identified acoustic signatures in the above predictive tasks. First, we will describe the expert labels by the percentage of sound labels attributed to each diagnosis. A multivariable logistic regression will be derived using the clinical data and sound labels to estimate the diagnoses, as for the primary objective. A kappa score will be used to assess the concordance between *DeepBreath* and expert diagnosis consolidated into a basic predictive model.

The K-BILD, CAT and SF-36 questionnaires will be analysed with descriptive statistics. Associations between the questionnaires’ sum scores and lung function parameters will be quantified by Spearman’s rank correlation coefficient. We will consider correlations < 0.3 as negligible, ≥ 0.3 to < 0.5 as low, ≥ 0.5 to 0.7 as moderate, and ≥ 0.7 as strong.

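### Two sections give different references for ILD severity (primary task 3), and the wider list lets a LUS-input model be scored against a human reading of its own examination

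*Protocol article*

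**What the plan says.** All references are to the protocol article.

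- **Primary and secondary outcomes** makes severity the third of four primary tasks: "to predict ILD clinical severity (according to a HRCT grading scale", followed by lung function tests. LUS is not named as a reference. The same paragraph makes LUS an input, since it will assess "algorithm-evaluated lung auscultation and LUS in the following identification and risk stratification tasks".
- **Diagnostic and risk stratification algorithms** states: "Risk stratification will use multiclass or regression according to scales obtained from clinical interpretation of LUS". The sentence goes on to lung function tests, HRCT, K-BILD or CAT, and SF-36. It ranks none of these and does not say which model input goes with which target.
- **LUS** (under Study procedure) has abnormal patterns reported zone by zone and a LUS score and normalised LUS score calculated for every patient. The images and clips for the models come from that examination.
- **Clinical assessment of lung auscultation and LUS** has external experts read the recorded LUS clips, blinded to clinical data and to the other modalities.
- **Primary hypothesis** includes the aim that automated interpretation should equal or better expert reading and make LUS interpretation more uniform.

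**The concern.** A primary task should have one reference standard. Here the outcome section gives two components and the algorithm section gives a longer list that includes readings of LUS. The extra LUS item is not neutral, because LUS is also a model input. If the model sees the images and the target is a person's reading of those images, or a score from the same examination, good agreement says little about disease severity. It says that the network has learned to read LUS as the human reader does.

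With several permitted targets and no ranking, the target closest to the input is likely to give the best figures. A severity result for task 3 could then rest on it and be read as evidence of risk stratification.

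**Working it through.** **1. Is there a figure to reproduce?** No. The article gives no numerical target for severity. Its one performance target, an AUROC above 80%, is set by analogy with a normal-versus-pathological sound task. The sample size (80 ILD + 40 COPD + 40 controls = 160) is not in dispute.

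**2. The two lists side by side**

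| Reference for severity | Primary and secondary outcomes | Diagnostic and risk stratification algorithms |
|---|---|---|
| HRCT | yes | yes |
| Lung function | yes | yes |
| Scales read from LUS | no | yes |
| K-BILD or CAT, SF-36 | no | yes |

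The lists agree on two items and differ on the rest.

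**3. Which combinations are circular?**

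| Model input | Target | Circular? |
|---|---|---|
| Sounds | HRCT, lung function | no |
| Sounds | LUS scale | no: the target comes from another modality |
| LUS images | HRCT, lung function | no |
| LUS images, alone or with sounds | LUS scale | yes |

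Only the last row is a problem. It arises by combining LUS as input (outcome section), LUS as target (algorithm section) and a score from the same examination (LUS section).

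**4. Do the plan's safeguards remove it?** Blinding the external readers keeps their readings free of the diagnosis and of the other modalities, but not free of the images. The fivefold cross-validation in the Statistical analysis plan guards against overfitting. In the held-out folds, however, the target is still a reading of the input.

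**5. How far could the result mislead?** Let q be the correlation of the model output with the LUS scale, and r the correlation of the LUS scale with severity measured independently. If the model's error around the LUS scale is unrelated to independent severity, the model's correlation with severity is q × r. The documents give neither q nor r, so both are assumed:

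| | r = 0.3 | r = 0.5 | r = 0.7 |
|---|---|---|---|
| q = 0.7 | 0.21 | 0.35 | 0.49 |
| q = 0.8 | 0.24 | 0.40 | 0.56 |
| q = 0.9 | 0.27 | 0.45 | 0.63 |

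An apparent 0.9 would stand for 0.27 to 0.63. If the network finds severity information in the images that the human reading misses, the true value could be higher. Only scoring against HRCT and lung function would show that.

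**The case against.** The strongest reply is that no sentence pairs LUS input with a LUS target. The line "The same prediction will also be made using LUS images" refers back to the binary diagnoses, and the risk-stratification sentence after it names no input. Where LUS is named as an input to severity prediction, the stated references are HRCT and lung function. The longer list includes CAT, a COPD instrument, so it may describe risk stratification in general rather than task 3. Learning to read LUS as an expert does is also a declared aim.

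Much of this stands. The pairing is an inference from three sections, LUS is one target among several, and automating LUS reading is legitimate under its own name. But the algorithm section does not set ILD severity apart from its wider list, so the list covers task 3 as written. A separate analysis plan could choose between the two statements, but the article would still contain both.

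Two stronger readings are tempting and are not supported:

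- A reader might infer that the reference standard leaks into the models generally. It does not. ILD v control, ILD v COPD and IPF v NSIP are judged against expert or guideline diagnosis, in which LUS is not named, and the main models for them take only sounds or LUS images.
- A reader might infer that the clinical-data models are fed the tests that define the groups. The plan will "explore the utility of adding clinical data (signs, symptoms, demographics, medical history and basic paraclinical tests) to the breath sound algorithms", and for the expert comparison "A multivariable logistic regression will be derived using the clinical data and sound labels to estimate the diagnoses", while controls are "individuals with normal lung function (spirometry, lung volume and transfer factor for carbon monoxide" and cases are already diagnosed. Yet nowhere is lung function, CT or the prior diagnosis said to be among these inputs. The paraclinical tests are not defined, the questionnaire is in an additional file not shown, and the analyses are secondary. No inflation of AUROC can be attributed to this on the documents.

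**Conclusion.** The inconsistency is real and confined to severity. The article gives two reference lists for primary task 3, and the longer one permits a circular evaluation of any model with LUS input. It should be settled before analysis. It does not undermine the study: the diagnostic tasks, sound-only prediction of a LUS scale, and LUS prediction of HRCT grade or lung function are untouched.

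The size of any overstatement cannot be taken from the documents. The 0.27 to 0.63 range rests on assumed correlations and on independent errors, and is illustrative. The conclusion itself needs no number, only that the outcome, algorithm and LUS sections are read together. The point about clinical inputs is a conditional safeguard, not a finding of error.

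**What to change.** In Diagnostic and risk stratification algorithms:

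1. State that HRCT grade and lung function are the references for primary task 3, as in Primary and secondary outcomes.
2. Keep K-BILD, CAT and SF-36 as secondary targets, reported separately.
3. Do not count a LUS-derived scale as a severity target for any model with LUS input, alone or combined with sounds. Report that analysis under its own label, *automation of LUS scoring*, linked to the agreement aim in the Primary hypothesis. A LUS scale may remain a target for sound-only models.

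As a subsidiary safeguard, if the history or paraclinical tests in the clinical-data models or the expert comparator turn out to contain the lung function that defines controls, or the prior respiratory diagnosis, leave those variables out.

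The cost is analysis wording only, with no new data, visits or patients. The severity performance of LUS models may look less favourable.

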**Fig. 2 Fig2:**
[figure not shown]
Overview of the DeepBreath binary classification model. Top to bottom: Data collection. Every patient will have 10 lung audio recordings corresponding to 1 per 10 anatomical sites (LAS, RAS: Left and Right Anterior Superior; LAI, RAI: Left and Right Anterior Inferior; LPS, RPS: Left and Right Posterior Superior; LPI, RPI: Left and Right Posterior Inferior; Left and Right Lateral [not shown on the figure]). Pre-processing. A band-pass filter is applied to clips before transformation to log-mel spectrograms which are batch-normalised and augmented and then fed into an audio classifier. Here, a CNN outputs both segment-level prediction and attention values which are aggregated into a single clip-wise output for each site. These are then aggregated by concatenation to obtain a feature vector of size for every patient, which is evaluated by a logistic regression. Finally, patient-level classification is performed by thresholding to get a binary output. The segment-wise outputs of the audio classifier are extracted for further analysis. Used with permission from Heitmann et al. (10.1038/s41746-023-00838-3, Nature Digital Medicine) (Swiss Federal Institute of Technology EPFL, Lausanne, Switzerland)

